### Sample size for co-primary and secondary outcome measures

This is the first study to utilise Cognition Support Formula® as a treatment for SCI, and thus there are limited comparable studies on which to base a sample size estimation. The most comparable study is by Lim et al. [34], who utilised a similar population (healthy older adults vs. people with MCI vs. AD) and a comparable measure to the current study as outlined in this protocol (CogState® battery). In order to see an improvement in performance in one test of the CogState battery® (group × time interaction) an effect size of Cohen’s *d* = .40 (i.e. Cohen’s *f* = .20, as *d* = 2*f*) at α = .05 was utilised [34].

To detect this effect size of Cohen’s *f* = .20 at α = .05 and 95% power, 100 participants across two groups are required. In order to account for a typical 20% drop-out, a total of 120 participants will need to be recruited (60 participants in the treatment group, and 60 in the placebo group). If the participation rate drops below the estimated number at any point during the course of the study, attempts to recruit additional participants will be made. Sample size may be re-estimated mid-course into the study to ensure adequate power. In this case, data will be unblinded by an objective third party to evaluate the treatment-effect size and power to assist with any potential sample size re-estimation.

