### Randomisation, allocation concealment, compliance and adverse effects

Participants will be randomly allocated at a 1:1 ratio to either the treatment or placebo group using a permuted block allocation strategy. Computerised randomisation and allocation will be conducted using a unique random number generator in Microsoft Excel by a university staff member external to the research team. This external staff member sent the random sequence directly to the trial drug manufacturer, with participant IDs and unique batch codes to conceal the sequence. This is a double-blind trial, so both participants and the research team are blinded to treatment allocation until study completion. After eligibility is confirmed, participants will then be allocated to the next participant ID/numbered box of product by a member of the research team. Compliance will be assessed by advising participants to return any unused medication at the midpoint (3 months) and endpoint (6 months), and by completion of a diary by participants noting medication intake and adverse effects.

To monitor safety, participants will be referred to a local commercial laboratory (Laverty) prior to baseline and the endpoint testing sessions. Standard blood safety tests (full blood count, fasting blood glucose, liver and renal function tests) will be carried out. If participants receive an abnormal blood safety test result at baseline, they will not be enrolled in the study and will be encouraged to follow up their results with their regular health professional. Adverse events will be closely monitored throughout the course of the study.

In the case of a serious adverse event, and if the study drug is suspected as a potential cause and identifying treatment allocation is essential to the participant receiving appropriate medical care, unblinding of that participant only will occur. This will be done by the university staff member external to the research team who generated the computerised random sequence allocation.

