### Statistical analyses and dissemination

For each participant in each group and at each timepoint the following data from the primary and secondary outcome measures will be assessed. For the CogState® detection, identification, one card learning, and one back tests, we will assess mean speed (ms), accuracy (%), and total number of hits, misses, and anticipations; for the Groton Maze test, we will assess the total number of errors; and for the mood (DASS-42, SHAI) and fatigue (FACIT-F) outcomes, we will assess subscale and composite scores. CogState® data that are not normally distributed will be transformed using logarithmic base 10 transformations. Generalised linear mixed models with a between-subject factor of group (treatment, placebo) and within-subject factor of time (baseline, midpoint, endpoint) will be conducted to assess differences in continuous co-primary and secondary outcome measures. Planned simple contrasts will be conducted to assess all timepoints (baseline vs. midpoint, midpoint vs. endpoint, and baseline vs. endpoint). To handle any missing data, analysis of last observation carried forward will be undertaken within the intention-to-treat analysis model. The premise of the intention-to-treat model includes all participants in the final analysis even if non-compliance, withdrawal, or deviation from the protocol occurs [38]. Due to the nature of drop-outs in clinical trials, this analysis will be carried out on all five primary and secondary outcome measures of cognition and secondary outcomes of mood (DASS and SHAI) and fatigue (FACIT-F).

All tests will be two-tailed, α = .05. MANOVAs and Pearson’s correlations may also be utilised for assessment of psychophysiological data depending on the outcome measures assessed. All data will be analysed using SPSS. Results from the trial will be presented publicly to the community through peer-reviewed journals and scientific conference presentations. Additionally, individual trial outcomes will be forwarded to participants, with their consent.

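### The drop-out allowance is miscalculated: 120 recruited with 20% loss leaves 96 completers, not the stated 100, though the cost in power is small

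*Protocol article*

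**What the plan says.** The section on sample size for the co-primary and secondary outcomes powers a group × time interaction at Cohen's f = .20 (d = .40) and α = .05, and concludes: "95% power, 100 participants across two groups are required". The next sentence inflates that number: "In order to account for a typical 20% drop-out, a total of 120 participants will need to be recruited", split as "60 participants in the treatment group, and 60 in the placebo group". The abstract repeats the total of 120.

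Two further provisions in the same section bear on the point. If participation falls below the estimated number, the team will try to recruit more. The sample size may also be re-estimated during the study. The section on statistical analyses plans an intention-to-treat analysis of all participants, with last observation carried forward (LOCF) for missing data.

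**The concern.** The three figures 100, 20% and 120 do not fit together. An allowance for drop-out should make the number recruited, less the expected loss, equal the number required. Here the loss has been added to the required number as a percentage of that number, when it should be taken as a percentage of those recruited. The result is a recruitment target that falls short of the plan's own requirement at the plan's own drop-out rate. At stake are the accuracy of the statement that justifies the trial's size and a small part of its power.

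**Working it through.** **Inputs, all from the main sample-size section**
- Required total: 100 (50 per arm; the randomisation section gives a 1:1 ratio).
- Drop-out: 20%.
- Recruited total: 120 (60 per arm).
- Effect size f = .20, α = .05, power 95%, group × time interaction.
- Not stated: the within-subject correlation ρ and the number of visits m used in the calculation.

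**Step 1. Reproduce the plan's figure.** 100 × (1 + 0.20) = 120. This matches exactly, so it is very likely how 120 was obtained.

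**Step 2. Check it against its purpose.**
- Expected completers: 120 × (1 − 0.20) = 96, or 48 per arm. Shortfall: 100 − 96 = 4.
- Number needed to retain 100: 100 / (1 − 0.20) = 125, or 126 for equal arms of 63.
- Drop-out that 120 actually covers: 1 − 100/120 = 16.7%.

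**Step 3. Size of the effect on power.** This step needs an assumption, because ρ and m are not given. I used the standard repeated-measures interaction F test for two groups: λ = f² × N × m / (1 − ρ), with (m − 1) and (N − 2)(m − 1) degrees of freedom. I chose ρ so that 100 is the smallest even N reaching 95% power.

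| Assumed setting | λ at N = 100 | Power at 100 | λ at N = 96 | Power at 96 |
|---|---|---|---|---|
| 3 visits, ρ = .25 | .04 × 100 × 3 / .75 = 16.00 | 95.4% | .04 × 96 × 3 / .75 = 15.36 | 94.6% |
| 2 visits, ρ = .40 | .04 × 100 × 2 / .60 = 13.33 | 95.1% | .04 × 96 × 2 / .60 = 12.80 | 94.3% |

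Other correlations also reproduce 100: about .235 to .25 with 3 visits, and .40 to .405 with 2. Across these, power at 96 runs from 94.1% to 94.6%, so the loss from 100 to 96 is under one percentage point.

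**Step 4. Sensitivity to the assumption.** With the same formula and 3 visits, power at 96 is 99.3% if ρ = .50. It is essentially 100% if ρ = .76, the lower end of the test-retest range that the article gives for CogState. At ρ = 0 it is 86.4%, but the requirement for 95% power would then be 132, not 100.

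**The case against.** The strongest reply is that nothing turns on four participants. On settings that reproduce 100, power at 96 is at most 0.9 points below the stated 95%. That stands, and it fixes the severity as low.

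A second reply is that the plan has safeguards. The top-up is a conditional attempt with no number attached. If the estimated number means 120, a trial that recruits 120 and then loses 20% need not trigger it. Re-estimation is optional. Both soften the consequence, but neither makes 120 the right allowance for 20%.

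A third reply is that intention-to-treat with LOCF analyses everyone randomised, nominally 120, so 96 is not the analysed number. That is fair as a description of the analysis set. But if drop-outs counted in full, no inflation above 100 would be needed; by inflating, the plan treats 100 as the number left after loss. Carried-forward values also do not supply the missing 6-month observations.

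A reader might go further and infer that the stated 95% power fails on the sponsor's own calculation. The documents do not support this: that calculation is not shown, the correlations in the table were back-solved, and a higher correlation would leave power at 96 well above 95%. A reader might also treat d = .40 as a plain two-group comparison and conclude that the trial is badly underpowered. That asks whether 100 was ever the right requirement for the interaction that the plan powers. It is a separate question from the drop-out allowance.

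**Conclusion.** The inflation is wrong as written. The head count follows from the article's own figures without any assumption: 96 expected completers against 100 required, and cover for 16.7% drop-out where 20% is claimed. No other definition of drop-out appears in the article that would reconcile the figures.

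The power consequence is conditional. It rests on a correlation and number of visits chosen to reproduce 100, and on counting completers only. On that basis the loss is about 0.8 points in each tabulated setting (95.4% to 94.6%, or 95.1% to 94.3%). This is a low-severity arithmetic error that does not undermine the design.

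**What to change.** Restate the sentence to say that 120 randomised allows for a drop-out of 16.7% and that, at 20%, 96 completers (48 per arm) are expected. Quote the power at 96, and give the within-subject correlation and number of visits used so that a reader can reproduce both that figure and the 100. Say in the same place that the intention-to-treat analysis includes all randomised participants, so that the completer figure is not mistaken for the analysis set.

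The cost is a sentence or two and perhaps a slightly less favourable stated power. The recruitment target and the analysis need not change.

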### Cognitive functioning evaluation

Participants will complete a number of computerised and pen and paper cognitive tests during the trial. Table 3 lists the cognitive, mood, and fatigue measures that will be utilised in this study. Further detail of these measures are given below.

The CogState® pre-clinical Alzheimer’s Battery of tests will be utilised to measure baseline, 3-month and 6-month changes in cognition. In addition to the battery, the Groton Maze learning test (CogState® test) will be completed by participants. CogState® is a computerised cognitive test battery that has excellent test-retest reliability ranging from .76–.93 (intra-class correlation coefficient) [34]. Participants will complete a practice trial prior to the main trial, in accordance with previous literature [34, 37]. There are no known practice effects associated with completing the practice. Practice trials will help to provide a ‘true baseline’ measure as errors are generally made during the first instance of completing the task. Participants will become familiar with the tasks during the practice trials, and this will therefore ensure equity in the measurement of task outcomes between the testing timepoints. The CogState® battery will be administered at baseline (0 months), the midpoint (3 months), and the endpoint (6 months), again with no known practice effects between time intervals. Furthermore, this cognitive testing method enables investigation into multiple areas of cognition including processing speed, attention, short-term memory, working memory, and executive function. The co-primary outcomes (one card learning and identification tests) measure visual short-term memory and attention, while the secondary outcomes (Groton Maze learning test, detection, and one back tests) measure executive functioning, processing speed, and working memory, respectively.

The DASS is a 42-item self-report instrument designed to measure the three related negative emotional states of depression, anxiety, and stress. Participants who consistently score higher than the normal range for depression (0–9), anxiety (0–7), or stress (0–14) (during baseline and midpoint sessions) will be advised to speak to their general practitioner. There is an expectation that participants will score higher in each of the three domains compared with a population without SCI [4].

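### The optional unblinded, effect-based sample size re-estimation is paired with an unadjusted α = .05, so the 5% type I error is not guaranteed if the option is used

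*Protocol article*

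**What the plan says.** Three statements in the protocol article bear on this.

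- *Sample size for co-primary and secondary outcome measures*: the planned size rests on f = .20 (d = .40), and "at α = .05 and 95% power, 100 participants across two groups are required"; 120 are to be recruited. The section then permits, but does not require, a mid-course re-estimation to keep power adequate. If it is done, "data will be unblinded by an objective third party to evaluate the treatment-effect size and power to assist with any potential sample size re-estimation".
- *Statistical analyses and dissemination*: "All tests will be two-tailed, α = .05". No exception is made for a trial whose size was changed after a look at the effect.
- *Randomisation, allocation concealment, compliance and adverse effects*: "both participants and the research team are blinded to treatment allocation until study completion".

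The re-estimation is therefore comparative. The quantity examined is the difference between the arms, not a pooled variance or correlation.

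**The concern.** When the final N depends on the interim treatment effect, the interim and later data are pooled with weights that depend on the interim result. The pooled statistic then no longer has its nominal null distribution. A rule that adds participants when the interim effect is weak, and leaves N alone when it is strong, dilutes unlucky starts and preserves lucky ones. Tested at the usual critical value, such a trial rejects a true null more than 5% of the time.

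At stake is the error rate of the two co-primary tests. The option is not far-fetched: the sample size section says there are few comparable studies to plan from. Once an ad hoc N based on the effect has been adopted, the error rate is hard to restore afterwards, because the rule that would have applied to other interim results is unknown.

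**Working it through.** **1. The plan's own figure.** For a group × time interaction with m repeated measurements and correlation ρ, λ = N·f²·m/(1 − ρ), with (m − 1) and (N − 2)(m − 1) degrees of freedom. The article does not state ρ for the sample size. With m = 3 and ρ = 0.25, λ = 100 × 0.04 × 3/0.75 = 16, and power at N = 100 is 0.954. So the stated 100 is obtained at ρ of about 0.25. With the same f, α and power, ρ = 0.5 gives N = 66 and ρ = 0.76 (the lower end of the test-retest range quoted under *Cognitive functioning evaluation*) gives 34. The stated N is thus very sensitive to a nuisance parameter that can be estimated without unblinding.

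**2. Why an effect-driven N matters.** Take n₁ per arm at the interim, N per arm at the end, and interim statistic z₁ under the null. The chance that the pooled test rejects in the upper tail is

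Φ(−[1.96√N − z₁√n₁]/√(N − n₁)).

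Planned N is 50 per arm. The interim size is not stated; take n₁ = 25. Reset N to N* = 2(1.96 + 0.84)²/d̂² with d̂ = z₁√(2/n₁), never reduced, capped at 75 (1.5 times plan).

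- z₁ = 1: d̂ = 0.283 and N* is about 196, so N becomes 75. At N = 50: (13.86 − 5)/5 = 1.77, probability 0.038. At N = 75: (16.97 − 5)/7.07 = 1.69, probability 0.045. The increase raises the error.
- z₁ = 2: d̂ = 0.566 and N* is about 49, so N stays at 50: (13.86 − 10)/5 = 0.77, probability 0.220. Had N been raised to 75: (16.97 − 10)/7.07 = 0.99, probability 0.162. An increase here would have lowered the error, but this rule makes none.

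The net effect is inflation. The same formula shows why a rule that increases N only after a promising interim result can be safe.

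**3. Overall error by simulation under the null.** Two-stage z-test, n₁ = 25, 30 or 40 of 50 per arm, N reset to give 80% or 95% power at the observed effect, increases only, final critical value 1.96:

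| Cap on N per arm | Two-sided type I error, unadjusted pooled test | Pre-weighted combination test |
|---|---|---|
| 75 (1.5 × plan) | about 5.1–5.7% | 5.0% |
| 120 | about 5.5–6.4% | 5.0% |
| none | about 6.7–7.9% | 5.0% |

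Repeat runs move the ends of these ranges by about 0.1 percentage point.

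**4. Sensitivity to the rule.** With the interim at 50% information, adding conditional-power rules to observed-effect rules (both increase-only) gives 5.3–5.7% at 1.5 times plan and 5.6–6.1% at 2 times plan. A late look (75%) with a conditional-power rule gives up to 6.0% at 1.5 times plan. Increasing N only when conditional power is at least 50% gives 4.4–4.9%: no inflation.

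**The case against.** **The look is optional.** This stands. If it is not used, nothing is inflated.

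**The full protocol or an analysis plan may hold the timing, rule, cap and test.** This stands for those details, and their absence from an article is not the point here. What the article does fix is the effect-based look and a general α with no exception. Any adjustment elsewhere would have to qualify that statement.

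**The inflation is small for a realistic expansion.** Largely right. Recruitment of 120 at one campus was already expected to run from September 2017 to late 2019, so very large increases are unlikely, and the uncapped figures are an upper range.

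**A third party does the unblinding.** This protects the team's blinding but not the error rate, since N depends on the interim effect whoever computes it.

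A reader might infer three stronger things that the documents do not support:

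- *That the final p-value would be invalid in every case.* Restricted rules can hold or undershoot 5%; the defensible statement is that control is not guaranteed.
- *That the look breaks the promised blinding, because the team could work back from a new N to the effect.* Blinding is promised for participants and the research team, and unblinding is assigned to someone else, so the two statements are compatible. With no stated rule and two co-primary tests, each with several metrics, a new N does not point to one effect.
- *That N might be cut, with larger inflation.* The stated aim is adequate power and the neighbouring text speaks of recruiting more, so reductions are outside what is planned.

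**Conclusion.** The concern holds in a limited form. As written, the article combines an optional comparative interim look that may change N with an unadjusted two-tailed α = .05, and this pairing does not guarantee a 5% type I error if the option is used. For increase-only rules that reset N from the observed effect, the excess runs from about 0.1–0.7 percentage points (cap at 1.5 times plan) to nearly 3 points (no cap).

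These figures assume the interim timing, the reset rules and the caps, none of which the article gives. They also assume a single outcome tested by a normal statistic with independent stages. Severity is moderate.

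**What to change.** Choose one of two routes and state it in the protocol.

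**A. Blinded re-estimation.** Replace the unblinded look with a re-estimate, at a fixed point, of pooled nuisance parameters only. Keep the planning effect fixed and set a maximum N. The useful parameter is the within-person correlation. Re-estimating the SD helps only if a raw target difference (in the units of the outcome) is stated first: the plan gives only a standardised effect, and with d = .40 held fixed a new SD changes nothing.

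**B. Keep the third-party unblinded look.** Fix in advance its timing, the outcome and rule that drive N, and the maximum N. Analyse the co-primary outcomes with a pre-weighted combination test (Cui–Hung–Wang): Z = √w·z₁ + √(1 − w)·z₂, with w = n₁/50 set from the planned per-arm size and z₂ from second-stage participants only. Qualify the general α statement accordingly.

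The cost is protocol wording, with the notification to the registry and ethics committee that the article already foresees for changes; route A also needs a raw target difference if the SD is to be used. The drawback of A is that a blinded review cannot correct an over-optimistic effect assumption. The drawback of B is a small loss of efficiency from the fixed weights.

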### Sample size for EEG sub-study

Most EEG studies do not utilise effect size calculations to determine sample size [35]. It is more important to determine signal-to-noise ratio in event-related potential (ERP) studies to ensure that the stimulus-evoked activity can be differentiated from the ongoing background EEG. Therefore, to obtain a meaningful EEG sub-study sample size (greater than 20 participants across both groups), the total sample size for EEG testing is 64 participants; 32 derived from the treatment group and 32 from the placebo group.

### Randomisation, allocation concealment, compliance and adverse effects

Participants will be randomly allocated at a 1:1 ratio to either the treatment or placebo group using a permuted block allocation strategy. Computerised randomisation and allocation will be conducted using a unique random number generator in Microsoft Excel by a university staff member external to the research team. This external staff member sent the random sequence directly to the trial drug manufacturer, with participant IDs and unique batch codes to conceal the sequence. This is a double-blind trial, so both participants and the research team are blinded to treatment allocation until study completion. After eligibility is confirmed, participants will then be allocated to the next participant ID/numbered box of product by a member of the research team. Compliance will be assessed by advising participants to return any unused medication at the midpoint (3 months) and endpoint (6 months), and by completion of a diary by participants noting medication intake and adverse effects.

To monitor safety, participants will be referred to a local commercial laboratory (Laverty) prior to baseline and the endpoint testing sessions. Standard blood safety tests (full blood count, fasting blood glucose, liver and renal function tests) will be carried out. If participants receive an abnormal blood safety test result at baseline, they will not be enrolled in the study and will be encouraged to follow up their results with their regular health professional. Adverse events will be closely monitored throughout the course of the study.

In the case of a serious adverse event, and if the study drug is suspected as a potential cause and identifying treatment allocation is essential to the participant receiving appropriate medical care, unblinding of that participant only will occur. This will be done by the university staff member external to the research team who generated the computerised random sequence allocation.

At the study midpoint, endpoint, and follow-up (7 months; 4 weeks after the endpoint) participants will be asked to which treatment condition they think that they have been allocated. Responses of Cognition Support Formula®, placebo, or unknown will be recorded. Responses will be checked against the condition allocated at the end of the trial after un-blinding. Participants who exit the trial early will also be contacted via telephone and asked to complete a trial exit interview pertaining to their experiences of the trial.

